## Materials and methods

3

### Study design

3.1

This study is an RCT examining the efficacy of PSG-T compared with PSG. The overview of the study design is summarized in Fig. 2.

**Fig. 2 fig2:**
[figure not shown]
Study design overview.

### Participants, inclusion and exclusion criteria

3.2

Eligible participants will be adults aged 18+ years who screen positive for PTSD on the Primary Care PTSD Screen for DSM-5 (PC-PTSD-5) related to a victimization trauma (e.g., physical assault, sexual assault, military combat) and who do not currently store all their personally owned firearms securely (i.e., unloaded and locked). See Table 1 for inclusion and exclusion criteria.

**Table 1 tbl1:** Inclusion and exclusion criteria and rationale.

Inclusion Criteria	Rationale
Aged 18 year or older	Population under study
Firearm owner	Population under study
History of one or more victimization traumas per the Life Events Checklist for DSM-5 (LEC-5), defined as having directly experienced physical assault, sexual assault, combat, and/or captivity	Treatment confound
Positive PTSD screen (Primary Care PTSD Screen for DSM-5 [PC-PTSD-5])	Population under study
Willing to provide physical location at time of Zoom sessions	Human subjects concern
Willing to keep Zoom camera on during study sessions	Human subjects concern
Ability to read, write, and speak English	Treatment confound

Exclusion Criteria	Rationale
Currently stores all personal firearms unloaded and locked	Intervention target
Active psychosis or acute mania necessitating clinical intervention	Human subjects concern
Acute thoughts of self- or other-harm necessitating imminent clinical intervention (e.g., hospitalization)	Human subjects concern
Known history of violent or threatening behavior toward hospital staff	Human subjects concern
Unable to provide informed consent	Human subjects concern

#### Ethical oversight

3.2.1

This study has been approved by the Colorado Multiple Institutional Review Board (COMIRB). The study has also been approved by the US Department of Defense's (DOD's) Office of Human Research Oversight. The trial has been registered at ClinicalTrials.gov (NCT06876740).

### Recruitment and informed consent

3.3

Participants will be recruited from clinics (e.g., outpatient mental health, primary care) affiliated with the University of Colorado Anschutz Medical Campus. Additionally, physical advertisements (e.g., flyers, brochures) and social media advertisements may be used. Interested participants will be directed to a study eligibility screening questionnaire. Eligible respondents will be contacted to schedule an appointment to describe the study, answer any questions, review the risks and benefits of the study, and ensure the participant understands the research. All study procedures will occur virtually over a HIPAA-compliant instance of Zoom, and informed consent will be obtained digitally through REDCap.

### Measures

3.4

Participant data will be gathered and stored via self-reported, web-based questionnaires using REDCap. See Table 2 for an overview of the assessments administered and their timelines.

**Table 2 tbl2:** Study measures by assessment period.

Study Assessments	Pre-Intervention	Post-Intervention	1-, 3-, and-6-Month Follow-Ups
Demographic and Military Service Characteristics	X		
Firearm Ownership and Storage Practices	X	X	X
Intentions to Store Firearms Safely	X	X	X
Firearm-Related Knowledge Questionnaire	X	X	X
Life Events Checklist for DSM-5 (LEC-5)	X		
PTSD Checklist for DSM-5 (PCL-5)	X		X
Posttraumatic Cognitions Inventory (PTCI)	X	X	X
Basic Psychological Needs Satisfaction and Frustration Scale-Single Items (BPNSFS-SI)	X	X	X
Depressive Symptom Index-Suicidality Subscale (DSI-SS)	X		X
Self-Injurious Thoughts and Behaviors Interview-Revised (SITBI-R)	X		X
Client Satisfaction Questionnaire-8 (CSQ-8)		X	X

#### Demographic characteristics

3.4.1

Participants will provide information about their age, sex, race/ethnicity, marital status, household composition, educational attainment, and military service experiences.

#### Firearm ownership and storage beliefs and practices

3.4.2

Participants will complete a comprehensive self-report measure of their firearm storage practices, including current use of firearm locking devices (both keyed and biometric devices), reasons for using or not using a locking device, likeliness that participant will encounter a situation that requires use of firearm, and likeliness to adhere to clinician's secure storage recommendations.

The primary outcome will be assessed by asking participants, “Thinking about the firearms in or around your home that you personally own, do you store them using any of the following methods?” Participants will be presented with two methods: “unloaded” and “locked.” For each method, they will be asked to indicate *Yes, all of my firearms*, *Yes, some of my firearms*, or *No, none of my firearms*. We assign a score of 2 if the secure practice applies to all firearms, 1 if it applies to some firearms, and 0 if it applies to none. A higher score corresponds to more secure storage practices. The maximum score, achieved when all firearms are both unloaded and locked, is 4, while the minimum score is 0. Improvement will be defined as a change score >0 between the pre-intervention and 6-month follow-up assessments.

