## Introduction

1

Firearm injury is the most common suicide method in the United States [1]. Dozens of case-controlled and ecological studies have shown that access to firearms is associated with increased suicide risk [[2], [3], [4], [5]]. The suicide risk conferred by firearm access persists even after accounting for other suicide risk factors, such as mental illness [[6], [7], [8]]. Among firearm owners, the way in which firearms are stored—for instance, loaded with ammunition and/or unlocked—may also associated with suicide risk [2,5].

To reduce the risk of firearm suicide, multiple stakeholders—spanning clinical, firearm industry, governmental, and non-profit sectors—recommend that firearms be stored securely [[9], [10], [11], [12]]. Secure firearm storage involves a range of possible behaviors, including storing a firearm unloaded, locked, separate from ammunition, and in a secure location [13]. Secure firearm storage can also include voluntarily moving a firearm out of the home for safekeeping with a friend, family member, gun shop, police station, or other community partner [14,15]. A prominent approach to encouraging secure firearm storage is delivery of lethal means safety counseling (LMSC). LMSC refers to guided discussions, often by a clinician, to encourage an at-risk individual to reduce access to firearms and other lethal methods of suicide [13,16].

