### Safety protocol

3.8

The study will be monitored by a Data and Safety Monitoring Board (DSMB). The DSMB includes four individuals with expertise spanning suicide prevention, firearm safety, PTSD, clinical trials methodology, and biostatistics. The DSMB will meet after the first 20 to 30 patients have been enrolled in the study, with subsequent meetings occurring every six months. If the DSMB or the investigator team determines that the risks of participating outweigh any potential benefits, the study may be discontinued.

Because all study procedures will take place virtually, including the intervention being delivered over the HIPAA-compliant Zoom platform, study staff will ensure that they have the participant's current location at the beginning of the consent visit and the intervention visit. Study staff will monitor for adverse events (AEs) and serious adverse events (SAEs), which will be reported to the IRB and DSMB according to standard practices. This trial is not specifically recruiting individuals with current or past suicidal symptoms (e.g., suicidal ideation, suicide attempts). However, as noted, all participants will complete the CRP intervention. We will follow standard clinical procedures if a participant were to report suicidal symptoms necessitating intervention (e.g., emergency rescue). We will also provide participants with a resource guide that lists information for national and local emergency services, crisis hotlines, a national map for out-of-home firearm storage and locations for purchase of locking devices.

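### The primary storage item gives no fitting answer or defined score to a participant who has moved every firearm out of the home

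*Protocol article*

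**What the plan says.** Section 3.4.2 of the protocol article (Firearm ownership and storage beliefs and practices) prints the item behind the primary outcome: "Thinking about the firearms in or around your home that you personally own, do you store them using any of the following methods". Two methods are offered, unloaded and locked. Each is answered for all, some or none of the participant's firearms and scored 2, 1 or 0, so the total runs from 0 to 4. The endpoint is binary: "Improvement will be defined as a change score >0 between the pre-intervention and 6-month follow-up assessments".

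Three other places bear on the scope of that item.

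- Introduction: "Secure firearm storage can also include voluntarily moving a firearm out of the home for safekeeping".
- Safety protocol (3.8): the resource guide given to participants includes "a national map for out-of-home firearm storage and locations for purchase of locking devices".
- Table 1, exclusion criteria: "Currently stores all personal firearms unloaded and locked". This refers to all personal firearms, without limiting them to those at home.

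The article states no response option or scoring rule for a participant who no longer has a firearm in or around the home.

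**The concern.** The Introduction treats removal from the home as a secure practice, and the trial tells participants where it can be done. In both arms the clinician and participant write a storage plan built on the participant's own goals, so removal is a possible result of either session. Hypothesis 1a concerns adoption of secure storage practices, yet the item that measures adoption loses its subject once no firearm is at home.

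Two things are at stake. First, the same behavior may be coded as failure, missing or success according to how each participant reads the question, which puts misclassification into the primary endpoint. Second, a blank left for this reason is missing because of what the participant did about storage. The primary model uses all available data and adjusts for covariates associated with missingness, which may not cover that. An answer option that was never offered cannot be fully rebuilt at analysis.

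A related gap sits at baseline. Exclusion and the primary item have different scopes, so a participant could in principle be randomized with a score of 4.

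**Working it through.** **1. Full removal by 6 months.** Let B be the baseline score, with B ≤ 3. Improvement requires (6-month score − B) > 0.

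| How the participant answers | 6-month score | Change | Coded as |
|---|---|---|---|
| None, for both methods | 0 + 0 = 0 | 0 − B ≤ 0 | Not improved, whatever B is |
| Leaves it blank | – | – | Missing |
| All, for both methods | 2 + 2 = 4 | 4 − B ≥ 1 | Improved, whatever B is |

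The printed text does not choose between these rows. All is a plausible answer because the response wording refers to the participant's firearms in general, and because no firearm at home is insecure.

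**2. Partial removal.** Take a participant with two firearms at home, one unloaded and locked, the other loaded and unlocked. The baseline score is 1 + 1 = 2.

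- Moving the insecure firearm out leaves all/all: score 4, change +2, improved.
- Moving the secure firearm out leaves none/none: score 0, change −2, not improved.

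The score therefore depends on which firearm stays, if the participant answers only for firearms at home.

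**3. Baseline score of 4.** The largest possible change is 4 − 4 = 0, which is never above 0. This could arise if the only insecure firearm is kept away from home, or if everything was secured between the screening questionnaire and the pre-intervention assessment. The Randomization section places allocation after that assessment, for participants who meet eligibility; the article does not say that the primary item is checked at that point.

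**4. Can an effect on power be derived?** The plan's own figure comes first. With 30% and 11.5% from the Power section, h = 2·arcsin√0.30 − 2·arcsin√0.115 = 0.467, which matches the stated 0.47. With 75 per arm and two-sided α = 0.05 (sidedness assumed), power = Φ(0.467·√37.5 − 1.96) = 82%. The ordinary two-proportion formula gives 80.4%, in line with the stated 80%.

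Next, suppose some improvers in those rates were really relocators coded as not improved. The shares are assumptions, since the article gives none.

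| Assumed loss (PSG-T / PSG) | Rates | h | Power, 75 per arm |
|---|---|---|---|
| None (relocators answer all) | 30% / 11.5% | 0.467 | 82% |
| 2 points / 2 points | 28% / 9.5% | 0.489 | 85% |
| 2 points / 1 point | 28% / 10.5% | 0.455 | 80% |
| 10% of improvers in each arm | 27% / 10.35% | 0.438 | 76% |

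The effect size can stay, rise or fall. The Power section also describes the 30% and 11.5% as new use of firearm locking devices, and moving a firearm out is not that, so nothing shows that relocators are in these rates at all. The table shows only that the answer is indeterminate.

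**The case against.** The strongest reply is that the trial's operational meaning of secure is stated, and it is unloaded and locked. It appears in the eligibility paragraph, in Table 1 and in the score. The out-of-home sentence is background, the map is one entry in a resource guide, and neither intervention description names transfer as a target. Limiting the endpoint to firearms at home is a defensible choice. That stands, but it does not settle how to score someone with none there.

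A second reply is that the article condenses a longer questionnaire, and branching or a rule may exist in the full instrument or analysis plan. That is possible and should be checked first. However, the item, its answers and its scoring are printed here and leave no place for this participant.

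A reader might infer three stronger things that the documents do not support:

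- *That a full relocator must score 0 or be missing.* An answer of all, scored 4, is equally open.
- *That the endpoint is biased against PSG-T.* This needs more transfers under PSG-T than under PSG, and nothing in the article says so.
- *That planned power is lost.* The planning rates concern locking devices, and an equal loss of 2 points per arm would raise h.

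On the baseline point, the reply that such participants arise before allocation, and so dilute rather than bias the comparison, is also fair. The article does not establish that any would be enrolled.

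**Conclusion.** The concern holds as a gap between the concept and the measured endpoint. A participant who has moved every firearm out of the home has no fitting answer and no defined score, and may be coded not improved, missing or improved. Partial moves can shift the score either way.

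The size and direction of the effect on the primary comparison cannot be determined from the article, because it gives neither the frequency of removal nor its split by arm. No loss of power is claimed. Severity is moderate: the defect touches the single primary endpoint and is hard to repair after data collection, but it may affect few participants. The conclusion assumes that the printed item is the full item and that no rule for this case exists in the questionnaire or analysis plan, neither of which is shown.

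**What to change.** 1. Add a response to the primary item at each assessment: *I currently have no personally owned firearms in or around my home*. Follow it with the reason: temporary safekeeping with another person or site, sold or given up, or kept elsewhere by the owner.
2. Before analysis, fix the scoring. Voluntary removal for safekeeping or disposal counts as improved; firearms that the owner keeps elsewhere are scored on unloaded and locked. The reasons must be kept apart, because giving the top score to every firearm held elsewhere would reward one kept loaded and unlocked at another place. State how partial removal counts as well.
3. Run a sensitivity analysis of the primary endpoint with the alternative coding.
4. Confirm a score of 3 or less on this same item at the pre-intervention assessment before randomization.

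The cost is one REDCap item, one scoring line and a minor amendment. The downside is small: some removals unrelated to counseling will count as improved, in either arm. If follow-up has begun, the change should be made soon, because status at past visits could then be recovered only from the rest of the questionnaire or from recall.

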#### Firearm-related knowledge

3.4.3

Participants will complete a questionnaire about the link between firearm storage practices and suicide risk.

#### Life Events Checklist for *DSM-5* (LEC-5)

3.4.4

The LEC-5 is a 17-item self-report measure of lifetime exposure to various traumatic events [31]. Participants indicate if each event happened to them, they witnessed it, they learned about it, it was part of their job, not sure, or does not apply.

#### Primary Care PTSD Screen for DSM-5 (PC-ptsd-5)

3.4.5

Consistent with the VA/DOD Clinical Practice Guideline (CPG) [32], we will use the PC-PTSD-5 to screen individuals at the eligibility determination stage. Participants respond Yes/No to five PTSD symptoms in the past month (score range: 0–5), and scores 4 or greater indicate a positive screen [33]. Individuals will complete the PC-PTSD-5 if they indicate they have experienced a victimization trauma, defined as physical assault, sexual assault, combat, or captivity (cf. LEC-5 items 6–11) [34].

#### PTSD Checklist for DSM-5 (PCL-5)

3.4.6

The PCL-5 is a 20-item self-report measure to evaluate PTSD symptoms over the past month [35]. Participants indicate how much they were bothered by PTSD symptoms from *not at all* to *extremely* in the past month (score range: 0–80). Consistent with the VA/DOD CPG [32], we will use the PCL-5 to monitor PTSD symptom levels across the study assessment timepoints.

#### Posttraumatic Cognitions Inventory (PTCI)

3.4.7

The PTCI is a 33-item self-report measure of PTSD-related negative cognitions about the self, world, and self-blame, which can occur following a traumatic event [36]. Participants indicate how much they agree or disagree on a 7-point Likert scale.

#### Basic Psychological Needs Satisfaction and Frustration Scale-Single Items (BPNSFS-SI)

3.4.8

The BPNSFS-SI is a 3-item self-report measure of self-determination theory constructs of autonomy, relatedness, and competence [37]. Participants rate each item on a 7-point Likert scale (score range: 3–21).

#### Depressive Symptom Index-Suicidality Subscale (DSI-SS)

3.4.9

The DSI-SS is a 4-item self-report measure of the severity of suicidal ideation over the past 2 weeks [38]. Participants rate each item on a 4-point scale (score range: 0–12).

#### Self-Injurious Thoughts and Behaviors Interview-Revised (SITBI-R)

3.4.10

The gate questions to each of the self-report SITBI-R modules will be used to evaluate suicidal thoughts and behaviors [39]. We will use the SITBI-R to assess history of these experiences at baseline and between-session experiences at follow-up assessments. Participants respond Yes/No to each item.

#### Client Satisfaction Questionnaire-8 (CSQ-8)

3.4.11

The CSQ-8 is an 8-item self-report measure that will be used to evaluate participant acceptability of the PSG-T intervention [40]. Participants respond to each item using varying descriptive scales with corresponding values.

### Randomization

3.5

Participants who meet eligibility criteria will be equally randomized between the two intervention conditions following the pre-intervention assessment. We will use computerized block randomization to allocate participants into either PSG-T or PSG. Block randomization will vary by the number of participants in each block to ensure that the research staff cannot anticipate the next randomization, which mitigates the potential for bias. Biostatisticians will oversee randomization. Neither study clinicians nor data analysts will be blinded.

### Intervention conditions

3.6

#### Project Safe Guard-Trauma (PSG-T)

3.6.1

PSG-T is a single-session, brief (20-min) LMSC intervention that promotes secure firearm storage practices among individuals with PTSD. PSG-T promotes secure firearm storage practices through MI [13,41] and by addressing the potential functional link between PTSD symptoms and non-secure storage practices [23]. MI-based LMSC focuses on respecting participants' autonomy, normalizing firearm ownership, and by guiding individuals to identify their values and motivations for secure firearm storage instead of prescribing specific actions. MI-based LMSC uses techniques to develop discrepancies, amplify ambivalence, express empathy, roll with resistance, and support self-efficacy [42]. PSG-T combines MI techniques from PSG [17], with a specific focus on gearing open-ended questions toward exploring the potential for trauma to have impacted one's storage practices and considering how enhancing secure firearm storage may be valuable. PSG-T also includes PTSD and firearm-specific psychoeducation, which focuses on the functional link between PTSD symptoms and firearm storage practices. The PSG-T clinician will work with the participant to generate a written plan for secure firearm storage, based on the participant's stated goals and intentions. A 1-page handout will be provided to participants recapping the points discussed (e.g., firearm-related harms, impact of trauma on firearm storage practices, firearm locking device options, written plan for secure firearm storage, and encouragement to share the document with someone else).

#### Project Safe Guard (PSG)

3.6.2

PSG is a single-session, brief (20-min) LMSC that promotes secure firearm storage practices using MI principles. The PSG clinician will work with the participant to generate a written plan for secure firearm storage, based on the participant's stated goals and intentions.

#### Crisis Response Planning (CRP)

3.6.3

Participants across study conditions will also receive crisis response planning (CRP) [43]. CRP is a brief intervention that helps individuals preemptively identify their personal warning signs for a crisis, coping strategies to implement, social supports to activate, and professional services to access. LMSC is not a component of CRP. CRP is associated with a reduced risk for suicide attempts and suicidal ideation, including in the context of PTSD psychotherapy [43,44]. CRP will be delivered in the same session as, and immediately before, PSG-T or PSG. For this trial, the narrative assessment component of CRP will not be used given the population under study is not selected for suicide risk. The decision to include CRP was twofold. First, in standard clinical practice, LMSC is commonly delivered in the context of CRP or safety planning interventions. Second, all participants will have screened positive for PTSD, and although suicidal ideation is not an inclusion criterion, risk of suicide is elevated in those with PTSD. Thus, including CRP as part of the intervention session will provide an added layer of risk mitigation.

### Quality control

3.7

#### Training and supervision of study interventionists

3.7.1

All study interventionists will have a master's or doctoral degree in clinical psychology and have experience in treating individuals with PTSD and suicide-related concerns. PSG training involves a 3-h session of didactic lectures from [name], a licensed clinical psychologist and the Principal Investigator (PI) on the initial PSG RCT. PSG-T training involves training in both PSG as well as an additional 1-h session of readings and didactic lectures from [name], a licensed clinical psychologist and the PI of this PSG-T RCT. All study interventionists will also receive guided readings on firearm laws relevant to the State of Colorado. Following training, study interventionists will receive up to approximately 60 min of weekly supervision or case consultation from the study investigators.

